### Inclusion and exclusion criteria

3.2

The inclusion criteria for this study are at least 18 years of age, diagnosed with MDD according to the Mini International Neuropsychiatric Interview 7.0.2 (MINI) that will be conducted by a trained research assistant. The MINI is a diagnostic interview that assesses 17 common mental disorders by following the diagnostic criteria of the Diagnostic and Statistical Manual of Mental Disorders, 5th edition (DSM-5) (41), ability to provide informed consent, ability to speak and read English, and having consistent and reliable access to the internet. The exclusion criteria include active psychosis, acute mania, severe alcohol, or substance use disorder, and active suicidal or homicidal ideation. Individuals with these disorders are less prone to having good insight into their thoughts; thus, e-CBT on their own may not be fit for them and would be better suited with therapist support throughout therapy. As for individuals with active suicidal or homicidal ideation, this program is not a crisis resource and individuals will be redirected to immediate support and resources that will better assist them. If a participant is receiving or has received CBT or e-CBT in the past year, they will also be excluded from the study to avoid confounding effects on the efficacy of this e-CBT program. If interested, participants excluded from the study will be linked to the appropriate resources.

### Study design

3.3

If eligible for this randomized controlled trial, participants (*n* = 186) will be randomized (Figure 1) to receive an e-CBT treatment recommended by a multi-professional healthcare team consisting of a psychiatrist, psychiatric medical resident, and a trained research assistant (Arm 1, control group; *n* = 93), or the AI machine learning algorithm (Arm 2, experimental group; *n* = 93; Figure 1). To ensure blinding, all participants will complete the intake assessment by the healthcare team (Arm 1) and the Triage Module (Arm 2). Only the relevant data (i.e., Arm 1: intake assessment vs. Arm 2: Triage Module) will be analyzed depending on the treatment arm that the participant is randomly assigned to.

**Figure 1 fig1:**
[figure not shown]
Study design flowchart for enrolment, arm allocation, and treatment intensity decision.

#### Treatment arm 1: healthcare team allocation

3.3.1

Allocation of treatment intensity by the multi-professional healthcare team will be based on the following criteria:

The severity of symptoms/disability (DSM-5 criteria).Mental health factors (prior treatments and responses, current and past psychotic/manic episodes, current and past suicidal/homicidal ideation/attempts, family mental health history, past psychiatric history, and hospital admissions).Medical factors (current medical conditions and medications, personal and family medical history).Social factors (support system and living situation, and occupational, social, and personal functional impairment).

To assess the severity of MDD symptoms and the functional impairments, participants will complete the PHQ-9 and Sheehan Disability Scale (SDS) (42, 43) before the assessment appointment. The trained research assistant on the multidisciplinary team will conduct the assessment appointment and will relay the information to the rest of the team later to deliberate on treatment intensity allocation. All assessments will occur virtually through phone and video calls. Together, the healthcare team will decide whether the participant should be assigned to the e-CBT-only treatment, e-CBT treatment with weekly phone/video calls, or e-CBT treatment with pharmacotherapy. This process mimics the current triage process in clinical settings. To track cost-effectiveness, the trained research assistant will track the total duration of the individual assessment and team deliberation meetings for analysis of the total time commitment per patient.

#### Treatment arm 2: AI algorithm allocation

3.3.2

Allocation of treatment intensity by the proposed AI algorithm will be based on the machine learning and natural language processing (NLP) of textual data provided by participants and their PHQ-9 score collected through a pre-treatment screening module called the Triage Module. This module, developed by the research team, (1) provides psychoeducation on the effects of psychotherapy, (2) collects PHQ-9 scores, and (3) asks participants six open-ended questions regarding their mental health history, their experiences with mental health disorders, and what mental health difficulties they are currently facing. Based on the participant’s answers to the open-ended questions, a variable called “Symptomatic Score” will be calculated using the NLP algorithm. If the PHQ-9 score < 19 and the Symptomatic Score > 0.75, the participant will be assigned to the e-CBT-only treatment group. However, if either the PHQ-9 score is >19 or the Symptomatic Score is <0.75, the participants will be assigned to the e-CBT treatment with weekly phone/video calls. If both scenarios occur and the PHQ-9 > 19 and Symptomatic Score < 0.75, then the participant will be assigned to the e-CBT treatment with pharmacotherapy. This NLP algorithm is patented by OPTT Inc. (International Patent System, PCT/US22/43514).

To gather the relevant data (i.e., participant compliance and change in depression severity, as evaluated by the PHQ-9), the Triage Module was designed. As previously explained, NLP of the participants’ written accounts of their challenges with depression in the Triage Module will be used to calculate a Symptomatic Score. To verify the AI’s treatment allocation logic, completion rate and the change in PHQ-9 scores in a sample of participants (*n* = 190) who were previously enrolled in e-CBT-only treatment was assessed. The decision-making algorithm determined that the e-CBT-only program was suitable for 62 of the 190 participants (32.63%). Within these 62 participants, 53.22% (*n* = 33) had completed the e-CBT-only program in its entirety and only 20% (*n* = 12) had a final PHQ-9 score > 14. Furthermore, the algorithm indicated that e-CBT with telephone calls would be suitable for 100 out of the 190 participants (52.63%). Of the 100 participants, 41.0% (*n* = 41) completed the whole round of e-CBT-only therapy and 31.0% (*n* = 31) had a final PHQ-9 score > 14. Lastly, the algorithm indicated that e-CBT with video call was appropriate for 28 out of 190 participants (14.74%). Of these 28 participants, 35% (*n* = 10) completed the whole round of e-CBT-only therapy and 40% (*n* = 11) had a final PHQ-9 score > 14. The logic of the AI’s decision is therefore justified as those participants allocated to the e-CBT-only group had the highest percentage of completion and lowest percentage of final PHQ-9 scores >14 when completing e-CBT-only. Therefore, minimal therapist intensity is required for these individuals and e-CBT-only is sufficient. Conversely, participants allocated to the e-CBT with video call had the lowest completion rates and highest rates of final PHQ-9 scores >14 when enrolled in e-CBT-only. These findings justify the AI’s logic that greater therapist interaction is required. It is also important to note that demographic factors like age (below or above 40 years), biological sex (male or female) and income (less or more than CAD 50,000) did not have any significant effects on the number of sessions completed by participants (*p* = 0.92, 0.18, 0.90 for age, sex, and income respectively). The demographic factors did not affect the change in PHQ-9 score (i.e., the difference between the beginning and end of treatment scores) either (*p* = 0.20, 0.46, 0.39 for age, sex, and income respectively).

### Treatment intensities

3.4

The three treatment intensities decided by the treatment arms (i.e., Arm 1: intake assessment or Arm 2: triage module using an AI algorithm) are:

e-CBT Program: The participant will submit their weekly homework and receive personalized feedback from their assigned therapist on the Online Psychotherapy Tool (OPTT). The feedback adds customization by acknowledging the participant’s experiences in the past week and ensures the participant has understood the CBT concepts.e-CBT Program + Call: In addition to the e-CBT program (see 1 above), the participant will receive a weekly phone/video call from their assigned therapist. The goal is to build on the therapeutic relationship and to add personalization with direct verbal encouragement. This phone call is limited to a one-time, 15–20-min call each intervention week (44). The purpose is to check with the patient on their treatment progress. The call will either be a secure phone or a video call, depending on the preference of the patient.e-CBT Program + Pharmacotherapy: In addition to the e-CBT program (see 1 above), the participant will receive standard pharmacotherapy following DSM-5 guidelines. A pharmacotherapy allocation system has been developed (Figures 2, 3) that follows clinical guidelines.

**Figure 2 fig2:**
[figure not shown]
The first phase of the drug-allocation process.

**Figure 3 fig3:**
[figure not shown]
The second phase of the drug-allocation process.

While pharmacotherapy in isolation has shown efficacy for the treatment of depression, this study focused on an e-CBT intervention with augmentation options (i.e., e-CBT vs. e-CBT + Call, vs. e-CBT + Call + Pharmacotherapy). Hence, no treatment arm with just pharmacotherapy was included in the treatment intensities.

### e-CBT platform

3.5

The web-based platform used for the study, the OPTT, is a secure, cloud-based, digital mental health platform (44). It complies with the Health Insurance Portability and Accountability Act, Personal Information Protection and Electronic Documents Act, and Service Organisation Control-2. In addition, all servers and databases are hosted in the Amazon Web Service Canada cloud infrastructure, which is managed by Medstack to ensure that all provincial and federal privacy and security regulations are met. OPTT does not collect any identifiable personal information or internet protocol addresses for privacy purposes. OPTT only collects anonymized metadata to improve its service quality and provide advanced analytics to the clinician team. OPTT encrypts all data, and no employees have direct access to participants’ data. All encrypted backups are kept in the S3 storage that is dedicated to Queen’s University, located in Kingston, Ontario, Canada.

### e-CBT program

3.6

The e-CBT sessions used in this study include content based on cognitive restructuring and behavioural activation techniques (45). The purpose of the sessions is to help participants become aware of inaccurate or negative thinking patterns so that they can view challenging situations more clearly and respond to them effectively. The sessions prompt participants to understand their situation/environment and the resulting thoughts, behaviours, physical reactions, and feelings. This program aims to help change participants’ negative and/or ineffective thoughts to more effective ways of thinking. As expressed in CBT, changing thoughts can subsequently affect feelings, behaviours, and physical reactions to stressful situations. The 13 e-CBT sessions are outlined below (Table 1).

**Table 1 tab1:** Session titles and descriptions for the e-CBT program.

Session	Description
*1 – What is Depression?*	Provides expectations for the course and introduces CBT and depression.
*2 – The 5-Part Model*	Introduces the concept of the 5-Part Model and how a situation, thoughts, feelings, physical reactions, and behaviours are connected and how they interact.
*3 – Sleep Hygiene*	Focuses on sleep habits and provides a variety of tips and strategies to use to increase sleep hygiene and get better rest.
*4 – Strategies for Stressful Situations*	Provides an overview of helpful strategies that can be used in stressful situations including pleasurable activities and helpful breathing techniques.
*5 – Thoughts, Feelings, Behaviour, Physical Reactions & Environment*	Provides a further detailed exploration of the 5 Part Model and how changes in one area can affect the other 4 parts.
*6 – The Thought Record*	Highlights the first three columns of the Thought Record; a tool used to help understand the connection between feelings, behaviours, and thoughts. The first three columns include the situation, followed by the feelings and automatic thoughts associated with the situation.
*7 – Automatic Thoughts*	This delves into the role of automatic thoughts and how they influence feelings. The focus of this session is to understand how to identify automatic thoughts and specifically identify the most dominant idea, or “hot thought” when presented with a stressful situation. Common thinking errors are also discussed in this session.
*8 – Activity Scheduling*	Provides a break from learning about the Thought Record and instead explains how to use an Activity Record; a tool designed to record and plan weekly activities. This session focuses on how tracking activities can inform mood changes and reinforce the scheduling of pleasurable activities.
*9 – Evidence*	Focuses on the fourth and fifth columns of the Thought Record, which is designed to help gather the information that supports or does not support the identified hot thought.
*10 – Alternative & Balanced Thinking*	Focuses on the final two columns of the Thought Record which reflects on the evidence columns to help find an alternative or balanced view of the situation. The last column invites the viewer to re-rate their feelings based on the completion of the Thought Record.
*11 – Experiments*	Explains the importance of conducting experiments to start believing alternative or balanced thoughts from the Thought Record and begin initiating changes in ineffective thinking patterns.
*12 – Action Plans*	Centred around identifying a problem that needs to be solved and provides a framework on how to create a plan for solving the problem.
*13 – Review*	The final session is a review of the course and summarizes the main CBT concepts and tools that have been taught throughout the program.

### Care provider

3.7

Each participant will be assigned a care provider who will provide feedback for their weekly sessions before the start of their next session. The assigned care provider will be independent of the multi-professional healthcare team that conducted the intake assessment. All care providers are trained in psychotherapy and have experience delivering electronic psychotherapy. They will be informed of each therapeutic session’s aim and content. They will also continue receiving specialized training through webinars, workshops and exercises with feedback provided by the lead psychiatrist on the research team, a trained and licensed psychotherapist (22, 46). All care providers will be supervised by a trained psychotherapist and the lead psychiatrist, and all feedback will be reviewed before submission to the participants.

### e-CBT weekly feedback

3.8

Weekly homework is reviewed by the independent care provider assigned to the participant, who will provide text-based personalized feedback on OPTT before the next weekly session. Participants and care providers can also communicate asynchronously on OPTT to relay any questions or concerns. The care providers will be provided with sample feedback templates and scripts for the telephone and video call sessions. Templates and scripts will be adapted from previous studies conducted by the research team. Feedback templates and scripts will vary between sessions, and care providers will personalize them for each patient. The feedback templates follow a generic structure starting with, acknowledging the participant’s time and effort since the last session, summarising the CBT concepts taught in the previous session, reviewing the event they explained in their homework, validating the participant’s experience(s), and encouraging the participant to keep up with the sessions. The feedback is written in a letter format to increase personalization and build rapport with the participants.

### Questionnaires & follow-up

3.9

Participants will complete a series of validated questionnaires at baseline including the Patient Health Questionnaire – 9 Item (PHQ-9), Sheehan Disability Scale (SDS), Quick Inventory of Depressive Symptoms (QIDS), Assessment of Quality of Life (AQoL-8D), and a demographic questionnaire. The PHQ-9 and QIDS questionnaire will be used to assess depressive symptoms and the AQoL-8D questionnaire will assess the participants’ quality of life. These three questionnaires provide insight into the participant’s mental status and perceived quality of life in the context of their depression. Additionally, the SDS will be used to assess the patient’s functional impairment for the clinician group assessment during baseline. During the program, participants will complete the PHQ-9 every 3 weeks (i.e., weeks 4, 7, 10, and 13), and the QIDS and AQoL-8D at weeks 7 and 13. All questionnaires (i.e., PHQ-9, QIDS, and AQoL-8D questionnaires) will be filled at the 3, 6, and 12-month follow-up periods to measure post-study outcomes.

### Sample size determination

3.10

In our previous clinical trials and gathered data (47), the average PHQ-9 score changed from 16.2 before e-CBT to 11.48 after 12 sessions of e-CBT (joint standard deviation; SD = 5.45). Based on these numbers, the effect size (Hedges’ G) is equal to 0.86. Given the effect size and a power of 0.8, we would need 14 participants to observe a significant effect in a paired sample *t*-test. Considering the completion rate of 45%, we would require 31 participants in each group to observe significant results. Given the two treatment arms and three treatment intensities, we would require 186 participants to detect significant clinical change across all groups. We believe this sample size is large enough to perform further analyses on factors such as the role of sex and gender in treatment efficacy and completion rate.

To follow up on this sample size determination, we will use previously collected data as mentioned above to simulate the population and use a random sampling method to determine the effect size for our power calculation. We will do this by simulating a population based on the mean and standard deviation of our previous e-CBT studies and collecting data, then randomly sampling participants to each treatment arm. This simulation will be developed using Python code. Based on this random sampling, we will calculate the effect size, set the power of 0.8, and consider the completion rate of 45% to determine the sample size required to detect a significant clinical change across the groups.

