## Statistical analysis

4

Initially, all data will be examined for missing, nonsensical, and outlying variables. Missing data will not be attributed and will be treated as missing. All statistical analyses will be performed at the end of the trial and will consider a significance level of 0.05 and 95% confidence intervals. Analyses will be conducted to account for and assess differences across sex and gender identifications, and how these factors affect the adaptability and efficacy of e-CBT.

### Hypothesis 1: outcomes in depressive symptoms of treatment arm 1 will be comparable to treatment arms 2 and 3

4.1

Clinical outcomes of the healthcare teams’ decision (arm 1) versus the AI’s decision (arm 2), will be compared by assessing the treatment completion rate, number of completed sessions, and change in questionnaire scores. The completion rate across the two study arms and three levels of care will be calculated using a 2 × 3 × 2 contingency matrix (i.e., healthcare team vs. AI × 3 different treatment intensities × completers vs. dropouts) and chi-square analysis to compare within and between completion rates in the two arms. We will use a 2 × 3 (i.e., healthcare team vs. AI × 3 different levels of care) two-way analysis of variance (ANOVA) to compare the number of completed sessions across participant groups and care levels. Questionnaires are collected at 3 different times; at the start (for all participants), midway (for those who completed at least 6 sessions), and end of the study (for those who completed the treatment program). We will use a 2 × 3 × 3 (i.e., healthcare team vs. AI × 3 different levels of care × 3 time points) linear mixed-effects model for each questionnaire to compare clinical outcomes within and between groups and times. A mixed-effects model analysis will account for any missing data caused by participant dropout. Finally, we will assess if demographic covariables affect clinical outcomes using multiple 2 × 2 × 3 × 3 (demographic factors (e.g., male vs. female) × healthcare team vs. AI × 3 different levels of care × 3-time points for the questionnaire’s score) mixed-effects model to account for each demographic variable (i.e., sex, gender, age, and income). Bonferroni corrections will follow the ANOVA analyses in *post hoc* analyses.

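### The sample size assumes 31 participants in each of six arm-by-intensity groups, but the plan's own triage data imply about 14 in the AI arm's top intensity, where power is about 0.4 instead of 0.8

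*Protocol article*

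**What the plan says.** Section 3.10 (Sample size determination) starts from earlier data: "the average PHQ-9 score changed from 16.2 before e-CBT to 11.48 after 12 sessions of e-CBT (joint standard deviation; SD = 5.45"). It says the effect size "is equal to 0.86" and continues: "Given the effect size and a power of 0.8, we would need 14 participants to observe a significant effect in a paired sample" t-test. It then allows for dropout ("Considering the completion rate of 45" per cent) and concludes that "we would require 31 participants in each group to observe significant results". Two arms times three intensities gives six groups and a total of 186, offered as enough to detect change in all of them. Section 3.1 (Participants) repeats 31 per e-CBT group in each of two arms. The same paragraph of 3.10 adds: "We believe this sample size is large enough to perform further analyses on factors such as the role of sex and gender".

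Sections 3.1 and 3.3 randomise participants to arm only, 93 to each. Intensity follows from the team's deliberation (3.3.1) or from cut-offs on the PHQ-9 and the Symptomatic Score (3.3.2). Section 3.3.2 also reports the algorithm's output for 190 people who had earlier received e-CBT alone: 62 to the lowest level, 100 to the middle, and for the third, "e-CBT with video call was appropriate for 28 out of 190 participants (14.74"%).

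Section 4.1 then analyses outcomes by arm and level of care, and adds demographic factors in 2 × 2 × 3 × 3 models.

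**The concern.** The power statement is made group by group, so it depends on each of the six groups reaching 31. The design controls arm size but not intensity size, and the only allocation figures in the article are far from equal thirds. If the trial resembles those figures, one AI-arm group gets less than half its planned number.

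At stake is how results in that group are read. A non-significant change in the top intensity could be reported as coming from a group with power 0.8 when the chance of detecting the assumed effect was about half that. Analyses that split the groups further, such as those by sex and gender, rest on the same equal-group picture.

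**Working it through.** **Inputs.** Effect size 0.86, power 0.8, completion 45%, 14 completers and 31 enrolled per group (3.10). Significance level 0.05 (section 4, which "will consider a significance level of 0.05 and 95% confidence intervals"); sidedness is not stated and is taken as two-sided. Arm size 93 (3.3). Triage split 62/100/28 of 190 (3.3.2).

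**Reproducing the plan's figures.**
- Effect size: (16.2 − 11.48)/5.45 = 4.72/5.45 = 0.866, stated as 0.86.
- Paired t-test with noncentral t (n − 1 degrees of freedom, noncentrality d√n), d = 0.86: 13 completers give power 0.812 and 14 give 0.844. The stated 14 is adequate.
- Enrolled per group: 14/0.45 = 31.1, stated as 31. Conversely 31 × 0.45 = 13.95.
- Total: 6 × 31 = 186.

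The arithmetic holds, provided the groups are equal.

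**Expected AI-arm sizes under the plan's own split.** Expected enrolled = 93 × share; expected completers = enrolled × 0.45.

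| Level | Share | Enrolled (planned 31) | Completers (planned 14) | Power, d = 0.86 |
|---|---|---|---|---|
| Lowest | 62/190 = 32.63% | 30.3 | 13.7 | 0.84 (n = 14) |
| Middle | 100/190 = 52.63% | 48.9 | 22.0 | 0.97 (n = 22) |
| Top | 28/190 = 14.74% | 13.7 | 6.2 | 0.40 (n = 6) |

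**Uncertainty in the share.** The 95% Wilson interval for 28/190 is 10.4% to 20.5%. Times 93, that is 9.7 to 19.0 enrolled; times 0.45, it is 4.4 to 8.6 completers. Power is 0.23 at n = 4 and 0.62 at n = 9. Averaging over binomial variation in the number of completers at the point estimate gives 0.40. With a true share of 14.74%, the chance that 31 or more of 93 fall in the top level is about 6 in a million.

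**Sensitivity to the effect size.** The 0.86 comes from e-CBT. If the added treatment in the top level raised it to an assumed 1.2, n = 6 would give power of about 0.66, still below 0.8.

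**Size needed for the stated plan.** To expect 31 in that level, the AI arm would need 31/0.1474 ≈ 210.

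**The case against.** Several points on the other side are fair.

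- *The trial's mix may differ.* The 190 had enrolled in e-CBT alone; this trial also recruits from hospital outpatient psychiatry clinics. That is a real limit on the point estimate. Still, these are the only allocation figures in the article, and the upper end of the interval (19) is well short of 31.
- *The level names do not match.* Section 3.3.2 reports the third level of the 190-person run as video calls, whereas the allocation rule in 3.3.2 and the list in 3.4 give pharmacotherapy. The match used here is by rank only. The passages must be reconciled.
- *The planned analysis uses more data.* The mixed model in 4.1 takes in partial data from dropouts and may recover some power. But the 0.8 in 3.10 is a completers-only paired-test figure, and it fails on those terms.
- *The follow-up simulation may correct this.* As described in 3.10, it samples people to treatment arms, not to intensities, and keeps 45% completion, so it would not reveal the unequal groups.

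Some stronger readings are tempting but unsupported:

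- A reader might apply the completion rates in 3.3.2 (33/62, 41/100, 10/28) and conclude that the top level will have even fewer completers. All 190 received e-CBT alone, so 10/28 does not forecast completion under a higher intensity. Pooled, the rates are (33 + 41 + 10)/190 = 84/190 = 44%, which supports the flat 45%.
- A reader might object that 31.1 should round up to 32. It has no consequence: 13 completers already give 0.81, and 13/0.45 = 28.9.
- A reader might infer that all six groups fall short. Two of the three AI-arm groups do not, and no split is given for the team arm. The arms themselves stay at 93 each.
- A reader might work out completers per sex in the top level. That needs a sex ratio the article does not give, and 3.10 claims no specific power for those analyses.

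**Conclusion.** The claim of power 0.8 in every group is wrong as written. On the plan's own triage data, the AI arm's top intensity would have about 14 enrolled and 6 completers, with power about 0.40; over the 95% interval for the share, about 0.23 to 0.62. The shortfall is confined to that group as far as the article allows one to say.

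The size rests on four assumptions: the trial's intensity mix resembles that of the 190; the third level of that run corresponds to the third level of this trial; completion is 45%; and d = 0.86 applies there. The completion assumption matters: if all 13.7 completed, power would be about 0.81 to 0.84. The more basic fault, that group sizes are treated as fixed when the design does not fix them, needs none of these assumptions.

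**What to change.** - In 3.1 and 3.10, replace 31 per e-CBT group with 93 per arm, and state that care-level sizes are not fixed.
- In 3.10, show the expected AI-arm sizes (about 30/49/14, top level 10 to 19) and state that no split is available for the team arm.
- Restate power in the AI arm's top level as about 0.4 (range 0.2 to 0.6), in place of 0.8 in every group, with the assumptions listed.
- Have the follow-up simulation draw intensity from the 62/100/28 split within the AI arm.
- Label the top-level results exploratory, likewise the sex and gender analyses (the 2 × 2 × 3 × 3 models), and amend the sentence that calls the sample large enough for them. The models themselves can stay.
- Reconcile the name of the third level within 3.3.2 and between 3.3.2 and 3.4.

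The cost is mainly wording, plus one added step in a simulation already planned. The stated power becomes less favourable; no extra participants are needed.

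### Section 3.10 gives every group the same effect size (0.86) and power (0.8), but the Arm 2 e-CBT-only group admits only PHQ-9 below 19, so 0.8 is not shown to hold there and is probably not met

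*Protocol article*

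**What the plan says.** Section 3.10 of the protocol article states that "the average PHQ-9 score changed from 16.2 before e-CBT to 11.48 after 12 sessions of e-CBT" ("joint standard deviation; SD = 5.45") and that "the effect size (Hedges’ G) is equal to 0.86". It continues: "Given the effect size and a power of 0.8, we would need 14 participants to observe a significant effect in a paired sample" *t*-test. It then inflates for a completion rate of 45%: "we would require 31 participants in each group to observe significant results". Multiplying by two arms and three intensities gives 186, presented as enough to detect change in all groups. Section 4 "will consider a significance level of 0.05 and 95% confidence intervals"; it does not say whether tests are one- or two-sided.

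Section 3.3.2 sets the Arm 2 rule. With PHQ-9 below 19 and a Symptomatic Score above 0.75, "the participant will be assigned to the e-CBT-only treatment group". One adverse criterion leads to the call level. Both together (PHQ-9 above 19 and score below 0.75) lead to the pharmacotherapy level.

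Section 3.10 also announces a follow-up simulation. As described, it draws from the overall mean and SD of earlier e-CBT studies and samples participants at random to the arms. It does not mention the intensity rule.

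**The concern.** PHQ-9 is both the variable whose change is powered and a variable that forms the Arm 2 groups. People chosen for a low baseline are expected to fall by less than the whole population, and people chosen for a high baseline by more, even if the treatment works equally well in both. One effect size cannot be assumed to hold in each such group.

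At stake is the claim of 0.8 power per group. Section 4.1 compares change within and between care levels over time. Without level-specific planning figures, a weak pre-post change in Arm 2 e-CBT-only and a strong one in the Arm 2 pharmacotherapy level could arise largely from selection. The question is separate from how many people reach each level: it remains even if e-CBT-only does receive 31.

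**Working it through.** **1. The plan's own figures.** Effect size: (16.2 − 11.48)/5.45 = 4.72/5.45 = 0.866, stated as 0.86. Paired t-test, two-sided 0.05 (assumed), noncentral t with n − 1 degrees of freedom and noncentrality d√n: n = 13 gives power 0.81 and n = 14 gives 0.845. Then 14/0.45 = 31.1, taken as 31, and 31 × 6 = 186. The chain reproduces closely enough.

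**2. Slack.** For power 0.8, 14 completers need d ≥ 0.81 (4.42 points at SD 5.45, 94% of 4.72). Section 3.3.2 reports 33/62 = 53.2% completion in earlier participants classed as e-CBT-only, so 31 × 0.532 = 16.5, about 16 completers. These need d ≥ 0.75 (4.08 points, 86% of 4.72).

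**3. Baseline after the cut.** Assume a normal baseline with mean 16.2 and SD 5.45, and a Symptomatic Score unrelated to PHQ-9 and to change.
- z = (19 − 16.2)/5.45 = 0.514; λ = φ(z)/Φ(z) = 0.350/0.696 = 0.502
- mean = 16.2 − 5.45 × 0.502 = 13.46
- SD = 5.45 × √(1 − 0.514 × 0.502 − 0.502²) = 3.81

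**4. Change after the cut.** With SD 5.45 at both visits and pre-post correlation ρ:
- mean change = 4.72 + (1 − ρ)(13.46 − 16.2)
- variance of change = (1 − ρ)² × 3.81² + 5.45² × (1 − ρ²)

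The overall SD of change is 5.45√(2(1 − ρ)). It equals 5.45, so that 0.86 is a paired effect size, only at ρ = 0.5. There the change is 4.72 − 0.5 × 2.74 = 3.35, its SD is √(3.64 + 22.28) = 5.09, and d = 0.66.

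| ρ | overall d implied | change | SD of change | d in group | power, n = 14 | power, n = 16 |
|---|---|---|---|---|---|---|
| 0.3 | 0.73 | 2.80 | 5.84 | 0.48 | 0.38 | 0.44 |
| 0.5 | 0.87 | 3.35 | 5.09 | 0.66 | 0.63 | 0.69 |
| 0.7 | 1.12 | 3.90 | 4.06 | 0.96 | 0.91 | 0.95 |

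Repeating this by simulation with scores rounded and limited to 0–27 gives 0.34, 0.59 and 0.90 with 14 completers, and 0.39, 0.66 and 0.94 with 16. At ρ = 0.5 the group needs 21 to 22 completers for power 0.8.

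**5. Narrower baseline spread.** Read 5.45 as the root mean square of the two visit SDs, and hold the overall SD of change at 5.45 so that 0.86 stays the overall paired effect.
- Baseline SD 4.5: end SD √(2 × 5.45² − 4.5²) = 6.26, group change 4.18, SD of change 5.39, d = 0.78, power 0.77 (14) or 0.83 (16).
- Baseline SD 4.0: d = 0.84, power 0.83 (14) or 0.88 (16).

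**6. A PHQ-9 floor.** An assumed minimum of 10 at ρ = 0.5 gives a baseline of 14.85, a change of 4.05, d = 0.83, and power 0.82 (14) or 0.87 (16). With rounded scores it is 0.78 and 0.84. Section 3.2 sets no such minimum.

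**7. The other end.** The same model for PHQ-9 above 19 gives d of about 1.6 at ρ = 0.5, against 0.87 overall, with no added treatment benefit assumed.

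**8. A rough check on ρ.** Section 3.3.2 reports final PHQ-9 above 14 in 12/62 (19%), 31/100 (31%) and 11/28 (39%) of the three classes. The rounded model predicts 23/29/42% at ρ = 0.3, 19/29/52% at 0.5 and 14/29/64% at 0.7. The data sit nearer 0.3–0.5. This is only indicative: the last class is small, and what counts as a final score is not defined.

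**The case against.** The best reply is that the documents give no change, SD of change or correlation by level, so any shortfall rests on a model. Truncation narrows the SD of change as well as the mean. If both scale with baseline, d stays at 0.866 and power with 14 completers at 0.85. A higher correlation, a baseline SD near 4 or a PHQ-9 floor also reaches 0.8, and the Symptomatic Score might select better responders. This stands, and it rules out stating the shortfall as fact. It does not rescue the plan's claim. The narrower SD is already in the working, ρ = 0.7 at the stated SD implies an overall effect of 1.12 rather than 0.86, and the floor is not an entry criterion.

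Three further points stand:
- **Scope.** A reader might infer that all six groups are cut at 19. Arm 1 is allocated on clinical criteria with no PHQ-9 cut (Section 3.3.1), and the Arm 2 call level takes people from both sides of 19.
- **Consequence.** A reader might infer that a non-significant change in e-CBT-only would count as failure of the AI triage. No hypothesis in Section 2 tests whether e-CBT alone suffices, and Section 4 names a mixed model, not a paired test per group.
- **Kind of error.** The 14, 31 and 186 are not miscalculated; the planning assumption behind them is in question.

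The planned follow-up simulation mitigates only in part, since as described it ignores the allocation rule.

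**Conclusion.** The point holds for Arm 2 e-CBT-only. The 0.86 is not shown to apply to a group restricted to PHQ-9 below 19, and the 0.8 is probably not met. Keeping the plan's 0.86 as the overall paired effect, with 5.45 at each visit, power is about 0.59–0.63 with 14 completers and 0.66–0.69 with 16. Over correlations of 0.3–0.7 with 14 completers it runs from about 0.34 to 0.91. The stronger statement, that this group certainly lacks 0.8, is not supported, because plausible assumptions fall on both sides.

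In the Arm 2 pharmacotherapy level the opposite is expected: a pre-post change inflated by selection. Nothing is quantified for Arm 1 or for the Arm 2 call level. The figures assume normal scores, a two-sided 0.05 level and a Symptomatic Score unrelated to change.

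**What to change.** - For Arm 2 e-CBT-only, replace 0.86 with the mean change, SD of change and completion seen in the 62 earlier participants whom the algorithm classed as e-CBT-only, and restate the power at the planned size.
- Apply the Section 3.3.2 allocation rule inside the planned simulation, so that each simulated Arm 2 level has its own baseline distribution and change.
- Do not take effect sizes for the call or pharmacotherapy levels from the other 128 earlier participants (190 − 62). All of them received e-CBT-only, and the highest class had only 10 completers. State those effects as assumptions with a range.
- Remove the statement that 186 gives the stated power in all groups.

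The cost is a re-tabulation of data the investigators already hold, a small change to the simulation and a corrected power paragraph. No extra patients are called for. The stated power for Arm 2 e-CBT-only will probably become less favourable: the change reports the power honestly but does not raise it.
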